**2.2 Secondary objectives:**

**Treatment-related adverse events (TRAEs):** The proportion of the treatment-related toxic reactions in the total evaluable cases according to the Common Terminology Criteria Adverse Events (CTCAE) 5.0.

**Out-of-field (abscopal) response rate (ASR):** At any time through enrollment to last follow-up, the longest diameter of any un-irradiated target lesions (per RECIST v1.1) reduce ≥30% will be considered as out-of-field (abscopal) response. The ASR is defined as the proportion of patients with an out-of-field response in the total evaluable patients.

**Overall survival (OS):** The time interval from enrollment to death due to any cause. Patients who are still alive at the time of analysis will be censored at the date of last contact.

**Progression free survival (PFS):** The time interval from enrollment to the first documented disease progression or death due to any cause. Patients who are still alive without disease progression at the time of analysis will be censored at the last date of last radiographic follow-up.

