Immune checkpoint inhibition (ICI) has revolutionized the treatment landscape of advanced NSCLC. Programmed cell-death protein 1 (PD-1) is an immune checkpoint molecule. PD-L1 and PD-L2, the ligands of PD-1, are up-regulated in a variety of tumor cells and tumor infiltrating cells. The interaction of PD-1 and its ligands (mainly PD-L1) can lead to the inhibition of cytotoxic T cells and the enhancement of regulatory T cells (Tregs), thereby inhibiting anti-tumor immunity. Sintilimab, a fully humanized anti-PD-1 monoclonal antibody, can block the interaction between PD-1 and PD-L1/PD-L2, subsequently induce strong anti-tumor response, which has confirmed *in vitro* and *in vivo*, with comparable affinity, pharmacokinetic characteristics and safety to pembrolizumab and nivolumab. For NSCLC, PD-1 monoclonal antibody nivolumab and pembrolizumab, as well as PD-L1 monoclonal antibody, atezolizumab and durvalumab, have all shown significant survival benefits when compared with the current standard of care treatments^[17-21]^. In the Keynote001 study, the ORR of pembrolizumab was 24.8% in untreated patients and 18.0% in previously-treated patients^[21]^. In the Keynote010 study, 1034 previously-treated advanced NSCLC patients were enrolled and divided into docetaxel group, low-dose pembrolizumab group and high-dose pembrolizumab group. An improved OS was observed in the high-dose pembrolizumab group compared with the low-dose pembrolizumab group and the docetaxel group (12.7 months vs 10.4 months vs. 8.5 months)^[22]^. In the PACIFIC study, durvalumab was used for unresectable stage III NSCLC without progression after standard platinum-based concurrent chemoradiotherapy. Durvalumab maintenance significantly prolonged PFS and OS compared with placebo^[20]^. However, the treatment efficacy of PD-1/PD-L1 inhibitors alone in unselected advanced NSCLC remain limited, with an ORR around 15%-20%, highlighting the crucial needs for the development of novel combinational treatment strategies with higher potency and less toxicity.

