**Figure 1. Study flow**

**Table 1. Study schedule**

|  | **Baseline screening** | **SBRT** | **Sintilimab, GM-CSF treatment** | **Sintilimab maintenance** | | **End of treatment**  **Survival follow-up** |
| --- | --- | --- | --- | --- | --- | --- |
| Window (days) | Within 28 days before the start of SBRT | End of SBRT  (or before D1 administration) | C1D1  D5/9/14 (± 2 days) | C2D1  (±3 days) evaluation before each administration | CnD1  (±3 days) | Every 3 months  (±7 days) |
| Frequency |  |  | 3 times in total | Every 3 weeks | Every 9 weeks  (every 3courses of Sintilimab) | Every 3 months |
| **Research procedure** |  | | | | | |
| Informed consent^1^ | X |  |  |  |  |  |
| Inclusion criteria | X |  |  |  |  |  |
| Demography/ Medical history/ Previous treatments^2^ | X |  |  |  |  |  |
| Vital signs ^3^ |  |  |  |  |  |  |
| Weight/Height^4^ | X |  |  | X | X |  |
| Medical history^5^/ Physical examination | X |  | X | X | X | X |
| ECOG PS score | X |  |  | X | X | X |
| Blood routine ^6^ | X |  | X | X | X | X |
| Coagulation function ^7^ | X |  |  | X | X | X |
| Blood Biochemistry ^8^ | X |  | X | X | X | X |
| Thyroid function ^9^ | X |  |  | X | X | X |
| Pregnancy test ^10^ | X |  |  |  |  |  |
| Urinalysis ^11^ | X |  |  | X | X |  |
| Virological antibody testing (HIV, HBV and  HCV) | X |  |  |  |  |  |
| 12-lead ECG | X | when necessary | | | | |
| Lung function | X |  |  |  |  |  |
| Adverse event assessment ^12^ |  | X | X | X | X | X |
| Concomitant medication | X | X | X | X | X | X |
| Subsequent anti-tumor treatment |  |  |  |  |  | X |
| Telephone follow-up (when outpatient follow-up is not possible) |  |  |  |  |  | X |
| **Efficacy evaluation** |  | | | | | |
| Radiographic assessment ^13^ | X |  |  |  | X | X |
| Gene mutation detection ^14^ | X |  |  |  |  |  |
| **Biomarker exploration** |  | | | | | |
| Blood specimens for biomarker studies ^15^ | X | X (end of SBRT) | X | X | X | X |
| Tumor puncture ^16^ | X | X (end of SBRT)  (Recommended, not required) | X (after d14 GM-CSF medication,  Recommended, not required) |  |  |  |

1. The signing of the ICF should be performed before any study procedure.
2. Previous treatments include treatment for the initial diagnosis, including chemotherapy, radiotherapy, and surgical treatment, as well as treatment for previous co-existing diseases within the past 30 days.
3. Vital signs include temperature, pulse, respiratory rate, and blood pressure.

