**6.3 Patient recruitment**

Assuming that the monthly recruitment rate is 4-5 patients, this trial is expected to complete the recruitment of patients 13-16 months after the start of the study. The last patient was followed up for another 25 months after enrollment.

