**6.5.2 Secondary endpoint**

**Treatment-related adverse events (TRAE):** Treatment-related toxic reactions according to the CTCAE 5.0.

**Out-of-field (abscopal) response rate (ASR):** Out-of-field response was defined as reduced by ≥30% of the longest diameter from baseline in any un-irradiated RECIST1.1 evaluable target lesions. ASR was defined as the percentage of patients achieving out-of-field response.

**Overall survival (OS):** The time interval from the first day of enrollment to death from any cause. Patients who are still alive at the time of analysis will be censored by the date of last contact until cut-off date. The Kaplan-Meier method will be used to estimate the survival curves of the two groups, and the median OS (90% two-sided confidence interval) will be calculated.

**Progression free survival (PFS):** The time interval from enrollment to the first documentation of disease progression or death due to any cause. Patients who are still alive without disease progression until data cut-off will be censored by the time of the most recent radiographic follow-up. The Kaplan-Meier method was used to estimate the survival curves of the two groups, and the median PFS (90% two-sided confidence interval) was calculated.

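### The out-of-field (abscopal) response window runs to last follow-up and does not stop at new anti-cancer therapy, so shrinkage caused by a later treatment can be counted

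*Protocol*

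**What the plan says.** Protocol section 2.2 fixes both the criterion and the period: "At any time through enrollment to last follow-up, the longest diameter of any un-irradiated target lesions (per RECIST v1.1) reduce ≥30" per cent. The denominator follows: "The ASR is defined as the proportion of patients with an out-of-field response in the total evaluable patients".

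Section 6.5.2 defines the endpoint again: "Out-of-field response was defined as reduced by ≥30% of the longest diameter from baseline in any un-irradiated RECIST1.1 evaluable target lesions". This version names baseline as the reference, which section 2.2 does not, and it gives no time window, which section 2.2 does.

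In Table 1, the column for end of treatment and survival follow-up (every 3 months) is marked both for the row "Radiographic assessment ^13" (the number is a footnote mark) and for the row "Subsequent anti-tumor treatment". On duration, section 6.3 says: "The last patient was followed up for another 25 months after enrollment".

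**The concern.** ASR is meant to describe what the study regimen does to lesions outside the radiation field. Under section 5.2, sintilimab stops at progression, among other reasons, and some patients will then start another treatment. If such a patient is scanned during follow-up and an un-irradiated target lesion has shrunk by at least 30% from baseline on the new drug, the section 2.2 wording makes that patient an out-of-field responder. The error runs one way: a later therapy can add responders but cannot remove any. A reader of the trial report would have no means of telling which responses came before the new treatment and which came after it.

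**Working it through.** **Plan's own figures.** The protocol gives no expected rate, threshold or decision rule for ASR, so there is nothing to reproduce for this endpoint. The only design figures, in section 6.1, concern ORR, and they reproduce by exact binomial calculation: P(X ≥ 17 | n = 56, p = 0.20) = 0.0432 and P(X ≥ 17 | n = 56, p = 0.38) = 0.908. ASR does not enter them.

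**Does anything in the protocol close the window?**

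- Section 2.2 ends it at last follow-up; section 6.5.2 does not mention an end.
- The ban on other anti-tumour treatment (the paragraph numbered 5.5.2, within 5.2.7) applies to the treatment period only.
- Section 3.3, item 8, makes receipt of other drugs that affect efficacy evaluation a ground for withdrawal. Exclusion from the efficacy analysis is stated only in items 1 and 3 of that list, and item 8 is not linked to the ASR window.
- Footnote 13 to Table 1 ties follow-up imaging to every third sintilimab course. The table nevertheless marks imaging in the survival follow-up column, and the footnote also calls for scans when new lesions are suspected at other times.

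None of these excludes a scan taken after a new therapy has begun.

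**Illustration of size.** All three inputs are assumptions, because the protocol gives none of them:

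- a = true ASR, meaning the proportion responding before any new therapy;
- f = proportion of the remaining patients who receive later therapy and are scanned on it;
- r = proportion of those with a shrinkage of at least 30% in an un-irradiated target lesion.

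Counted ASR = a + (1 − a) × f × r. With a = 0.20:

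| f | r | Counted ASR |
|---|---|---|
| 0.30 | 0.05 | 0.20 + 0.80 × 0.30 × 0.05 = 0.212 |
| 0.30 | 0.20 | 0.20 + 0.80 × 0.30 × 0.20 = 0.248 |
| 0.50 | 0.05 | 0.20 + 0.80 × 0.50 × 0.05 = 0.220 |
| 0.50 | 0.20 | 0.20 + 0.80 × 0.50 × 0.20 = 0.280 |

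The excess is 1.2 to 8.0 percentage points. If 56 patients are evaluable, that is 0.012 × 56 = 0.7 to 0.08 × 56 = 4.5 patients. With a = 0.30 the same ranges give 0.30 + 0.70 × 0.30 × 0.05 = 0.3105 up to 0.30 + 0.70 × 0.50 × 0.20 = 0.370.

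**The case against.** The best defence on the window is that the schedule does not prove such scans will be taken. Imaging in survival follow-up also serves patients who stop without progression, for toxicity or after 35 cycles, and withdrawal under section 3.3 may end imaging for some who start other drugs. This stands as a limit: later-therapy responses can be counted, not that they will be. It does not remove the problem, because section 2.2 states the long window outright. It is not a silence that a statistical analysis plan could fill; a plan that stopped earlier would contradict the protocol.

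Three stronger readings are tempting, and the documents do not support them as defects.

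- **Any single lesion.** A patient qualifies even if other lesions grow. With lesions going from 20 to 14 mm and from 40 to 52 mm, the sum rises from 60 to 66 mm (+10%), yet the patient is a responder. But both sections state the any-lesion rule consistently, and it is a defensible lesion-level measure; patient-level response by RECIST is already the primary endpoint. If each lesion had an assumed 20% chance of shrinking, the patient-level rate would be 1 − 0.8^k: 20% with one lesion and 59% with four, if lesions were independent. With perfect correlation it would stay at 20%. The protocol gives no per-lesion rate, so this shows only that the measure depends on lesion count.
- **Lymph nodes.** Objecting to longest diameter for nodes relies on a RECIST measuring rule that the protocol does not reproduce, and both definitions refer to RECIST 1.1.
- **Attribution to radiotherapy.** The background reports PD-1/PD-L1 inhibitors alone in unselected patients "with an ORR around 15%-20" per cent, so sintilimab could itself shrink un-irradiated lesions. That is a limit of any single-arm combination trial, and redefining ASR would not cure it.

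**Conclusion.** The concern holds for the time window. As section 2.2 is written, and with nothing in section 6.5.2 to narrow it, shrinkage after the start of a new anti-cancer therapy can count as an out-of-field response to the study regimen. The direction of the bias is upward and follows from the wording alone. Its size cannot be derived from the protocol; the 21.2% to 28.0% range against a true 20% rests wholly on the assumed shares above. The two definitions also differ on window and reference measurement and need to be aligned.

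The consequence is confined to a secondary endpoint without a hypothesis or threshold. A reader might infer that the trial's success criterion is compromised; it is not, because the rule of 17 responders among 56 patients uses ORR only.

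**What to change.** Use one definition in sections 2.2 and 6.5.2: change is measured from baseline, and only scans taken before the start of any new anti-cancer therapy count, whether that therapy is systemic or local to the assessed lesion. The any-lesion criterion can remain as the definition of ASR.

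As a supplementary descriptive analysis, report the rate of a decrease of at least 30% in the sum of diameters of the un-irradiated target lesions, without new lesions or progression.

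The cost is a wording change in two sections. Lesion imaging and subsequent treatment are already in the schedule, so no new data are needed. The downside is that the reported ASR may be lower.

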**3.3 Subject withdrawal/discontinuation criteria:**

1. Inappropriate enrollment. Those who have not received any treatment after enrollment should withdraw immediately, and the subject's information will not be included in the study analysis. If the subject has already received study treatment, the investigator will evaluate the subject and determine the benefit and risk of the subject before deciding whether to withdraw. If the subject needs to be excluded, he/she will be withdrawn from the study after the completion of follow-up after treatment. The subject’s information will not be included in the efficacy analysis of this study, but should be included in the safety analysis.
2. Any of the following situations occur during the pre-treatment evaluation stage: new or deteriorated systemic disease which meet the exclusion criteria, voluntarily withdraw consent or lost to follow-up or death; poor compliance.
3. For those who are considered to be excluded by investigators, the investigator shall report the reasons for the exclusion to the principal investigator. When permitted, patients who have not yet received any study treatment should be withdrawn immediately, and the information of this subject will not be included in the study analysis. If the subject has already received the protocol specified treatment, he/she will be withdrawn from this study after the completion of the follow-up after treatment, and the subject will not be included in the efficacy analysis of this study, but should be included in the safety analysis.
4. Subjects may request withdraw from the clinical trial at any time during the study period if they do not want to continue.
5. If serious adverse events occur, the subject might be withdrawn on the judgment of the investigator.
6. Deterioration during the trial, which may threaten the life of the subject, or other conditions that may affect the observation appear during the trial.
7. The subject lost follow-up or die during the treatment period.
8. The subject received chemotherapy, Chinese medicines, other immunotherapy drugs, radiotherapy sensitizers, or other drugs that affect the efficacy and toxicity evaluation during the trial.
9. Serious deviations which makes it difficult to evaluate the drug effect.
10. Poor compliance.
11. **Study plan and timing of procedures**

[figure not shown]

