5.5.2 Prohibited concomitant treatment

Subjects are prohibited from receiving the following treatments during the treatment period of this study: Biological therapy with anti-tumor effect (except for cytokine drugs used to treat adverse events caused by chemotherapeutic drugs), and proprietary Chinese medicines with anti-tumor effect; Drugs with immunomodulatory effects, including but not limited to non-specific immunomodulators (such as thymosin, interferon, interleukin, immunoglobulin, gamma globulin) and Chinese patent medicines with immunomodulatory effects, etc. Chemotherapy not specified in this regimen. Live vaccination within 30 days before the first administration of Sintilimab and during the study. Live vaccines include, but are not limited to, the following: measles, mumps, rubella, varicella, yellow fever, rabies, BCG, typhoid (oral) vaccine. It is allowed to receive inactivated virus vaccines against seasonal influenza, but it is not allowed to receive live attenuated influenza vaccines for intranasal inoculation. Corticosteroids. Allows the use of inhaled steroids as part of a fixed treatment for asthma or chronic obstructive pulmonary disease (COPD). Allows corticosteroids to be used in the treatment of adverse events with underlying immune causes. After consultation with the sponsor, the use of physiological doses of corticosteroids can be approved. Note: Prophylactic corticosteroids are allowed to avoid allergic reactions (for example, pretreatment prior to administration of intravenous contrast agents or chemotherapy drugs). According to the investigator's assessment, subjects who need to use any of the above treatment methods for clinical treatment should be excluded from the trial. Subjects can receive other medications deemed medically necessary by the investigator. It is important for researchers to review each drug (prescription and over-the-counter) that subjects received before the start of the study and during each study visit. At each visit, the subject must be asked about any new drugs received. In order to reduce the risk of adverse drug interactions, all measures must be taken to limit the number of concomitant medications that are really necessary. During the administration period, you should avoid receiving hepatotoxic drugs (that is, drugs that are warned of hepatotoxicity in the product instructions). Researchers are encouraged to [review each](http://www.livertox.nih.gov/) potential hepatotoxic drug by searching the www.livertox.nih.gov website.

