**New anti-tumor treatment**

Within 90 days of the last administration, if the subject starts a new anti-tumor treatment, only serious adverse events related to the study drug will be recorded and reported.

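### The abscopal response rate has no cut-off at new anti-tumor therapy, so shrinkage on a later treatment counts as a response to the study regimen

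*Protocol*

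**What the plan says.** Section 2.2 (Secondary objectives) counts an out-of-field response by the rule "At any time through enrollment to last follow-up, the longest diameter of any un-irradiated target lesions (per RECIST v1.1) reduce ≥30" percent. The denominator is all evaluable patients. Section 6.5.2 restates the endpoint for the analysis: "Out-of-field response was defined as reduced by ≥30% of the longest diameter from baseline in any un-irradiated RECIST1.1 evaluable target lesions". It adds the baseline reference and gives no start or end to the counting period.

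The last column of Table 1 (end of treatment and survival follow-up, every 3 months) marks both "Radiographic assessment" and "Subsequent anti-tumor treatment". Section 6.3 follows the last patient for 25 months after enrollment. Under section 5.2, sintilimab ends at progression, death, unacceptable toxicity, withdrawal of consent or 35 cycles.

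Three other places deal with non-study anti-tumor treatment:
- Section 3.3, criterion 8, lists as a ground for withdrawal or discontinuation: "The subject received chemotherapy, Chinese medicines, other immunotherapy drugs, radiotherapy sensitizers, or other drugs that affect the efficacy and toxicity evaluation during the trial".
- Section 5.5.2 (numbered so, within 5.2.7) opens its ban with "Subjects are prohibited from receiving the following treatments during the treatment period of this study".
- Section 7.4.3, under the heading on new anti-tumor treatment, says of the 90 days after the last dose that "if the subject starts a new anti-tumor treatment, only serious adverse events related to the study drug will be recorded and reported".

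**The concern.** ASR is meant to show whether the study regimen induces responses outside the irradiated field, so it is the endpoint closest to the trial's rationale. Once a patient moves to another active treatment, shrinkage of an un-irradiated lesion may be due to that treatment. A window that runs to last follow-up still credits it to the regimen.

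One lesion in one patient is enough to count. The bias has a fixed direction: a later therapy can turn a non-responder into a counted responder, but it cannot remove a response already recorded. In a single-arm trial there is no control group in which the same inflation would show.

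The concern does not extend to shrinkage after RECIST progression but before any new therapy. ASR is judged lesion by lesion, and the study regimen may have caused that shrinkage.

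**Working it through.** **1. Does the plan state a figure for ASR?** No. It gives no threshold, sample size, alpha or power. The only design figures are for ORR in section 6.1, and they reproduce by the exact binomial:
- P(X ≥ 17 | n = 56, p = 0.20) = 0.0432, as stated.
- P(X ≥ 17 | n = 56, p = 0.38) = 0.908, in line with the stated power of at least 90%.
- 56/(1 − 0.10) = 62.2, rounded up to 63, as stated.

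These supply the two denominators used below, 56 and 63.

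**2. Can a scan on later therapy fall inside the window?**
- Window: enrollment to last follow-up in 2.2; none stated in 6.5.2.
- Imaging after study treatment: marked in the follow-up column of Table 1.
- Later therapy: recorded in the same column.
- Time available: a patient who stops at the first nine-weekly evaluation can have most of the 25 months of follow-up still ahead.

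Such a scan is therefore possible under the schedule and lies inside the window.

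**3. Does any other text end the counting?**
- Criterion 8 in 3.3 gives a reason to withdraw. It states neither an assessment cut-off nor removal from the efficacy analysis. Criteria 1 and 3 do state removal; criterion 3 says "the subject will not be included in the efficacy analysis of this study, but should be included in the safety analysis". Where the protocol intends that consequence, it says so.
- The ban in 5.5.2 ends with the treatment period.
- The rule in 7.4.3 applies to adverse event recording only.

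None of them closes the window.

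**4. What must happen for a false response to count?** The patient must have had no out-of-field response before the new therapy, and one un-irradiated target lesion must then measure at least 30% below baseline. If that lesion had grown by a fraction g when therapy changed, it must shrink by 1 − 0.70/(1 + g) of its size at that time. This is 30% when g = 0 and more when g > 0. The case g = 0 is realistic: a patient can progress through a new lesion while a target lesion stays near its baseline size.

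**5. Effect per event.**

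| Events | of 56 | of 63 |
| --- | --- | --- |
| 1 | 1/56 = 1.79 points | 1/63 = 1.59 points |
| 3 | 3/56 = 5.36 points | 3/63 = 4.76 points |

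The count of one to three is an assumption.

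**6. Wider illustration, all inputs assumed.** Let a be the true ASR, s the share of non-responders imaged on a later therapy, and q the chance that such a therapy takes an un-irradiated target lesion at least 30% below baseline. Then counted ASR = a + (1 − a) × s × q. With a = 30%:
- s = 30%, q = 5%: 0.30 + 0.70 × 0.30 × 0.05 = 0.3105, or 0.0105 × 56 = 0.6 extra responders.
- s = 70%, q = 20%: 0.30 + 0.70 × 0.70 × 0.20 = 0.398, or 0.098 × 56 = 5.5 extra responders.

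With a cut-off at new therapy, the estimate would stay at 30% in both cases.

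**The case against.** The best defence is that rules for scans after subsequent therapy usually belong in a SAP, and that this protocol gives none for ORR or PFS either. On that reading, the long window in 2.2 is only an outer limit, set so that late responses are not missed. This would carry weight if the protocol were silent. It is not: 2.2 writes the window out, and a SAP that closed it would contradict the protocol.

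Criterion 8 can be read as ending efficacy evaluation once another drug is given, since its stated reason is interference with that evaluation. The reading is reasonable but is not what the text says, and Table 1 keeps imaging and later therapy in the same follow-up phase.

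The imaging mark in that column might mean only an end-of-treatment scan, and footnote 13 ties follow-up imaging to every three courses of sintilimab. No text requires scans after progression, so such scans are possible rather than certain. But the column runs every 3 months, and nothing limits its imaging to patients without new therapy.

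Two points stand. Measuring from baseline makes false responses rarer, and no decision rule depends on ASR. Both limit the size of the problem without removing it. The comparison with the safety rule in 7.4.3 proves nothing about efficacy; it shows only that the authors considered new therapy in one place and not in the other.

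**Conclusion.** The concern holds. The ASR rule as written credits shrinkage on a later anti-tumor therapy to the study regimen, and it can bias the estimate only upward. The firm figure is the effect per event: 1.8 points with 56 evaluable patients, 1.6 points with 63. The number of events cannot be derived from the protocol, so the ranges of 1.8 to 5.4 points (56 patients) and 1.6 to 4.8 points (63 patients) rest on an assumed one to three events. The shift from 30% to about 31–40% rests on assumed values of a, s and q. ASR is secondary and descriptive, and the ORR success rule is untouched. The definition should be corrected, but the flaw does not threaten the trial's main conclusion.

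**What to change.** In sections 2.2 and 6.5.2, count in the main ASR only reductions of at least 30% from baseline that are documented before the start of any new anti-tumor therapy, meaning systemic therapy or local therapy to the lesion concerned. Report reductions first seen after that point in a separate table. Keep reductions that occur after RECIST progression but before new therapy in the main ASR, and flag them in the table. A stricter option would also stop at progression, but that suits a lesion-level endpoint less well because it discards shrinkage the regimen may have caused.

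The cost is wording in two sections and one extra table, with no extra patients or scans. The main ASR may come out slightly lower, and a true late abscopal response first seen after new therapy has begun will appear only in the separate table.
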